### Procedure

Eligible participants are recruited from outpatient clinics from three academic hospitals and four non-academic hospitals, representing the major regions of The Netherlands. Children and parents receive an information letter from the pediatrician and posters and pamphlets are available at the clinic. Recruitment is coordinated by local investigators of each hospital. Parents and children are asked to read the information and, if interested to participate, to return an application form in a stamped self-addressed envelope. Then informed consent forms are sent to be signed by both parents and child, and within 2 weeks, a telephone interview is used to check inclusion criteria. Eligible participants are randomized to either the interventions or the wait-list control condition, and are informed about the randomization outcome by letter. In all conditions assessments take place at baseline, 6 weeks, 6 months and 12 months after baseline. Within a month after the baseline measurements, the intervention starts. Families receive a financial reward (€65) for completing assessments, spread across the four measurement points but increasing in amount at each follow-up.

Interventions are conducted by two child psychologist or by a psychologist and a psychological assistant working in the participating hospitals. The intervention is described in a manual, session by session. A protocolled training is given to all psychologists. This training consists of three parts 1) teaching the main principles of cognitive-behavioral group therapy, 2) giving more specific information on the procedures and goals related to the different sessions using video examples and the extensive manual for psychologists, 3) practicing a number of assignments to enlarge their preparation for giving the intervention. To ensure treatment integrity, randomly selected therapy sessions are recorded on audiotape or videotape, and coded afterwards following the procedure of Wood et al. [16].

Figure 1 depicts the different stages of the research procedure.

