**Methods/design:**

This study is a multicentre randomized controlled trial. Participants are children (8 to 18 years of age) with a chronic illness, and their parents, recruited from seven participating hospitals in the Netherlands. Participants are randomly allocated to two intervention groups (the child intervention group and the child intervention combined with a parent program) and a wait-list control group. Primary outcomes are child psychosocial functioning, wellbeing and child disease related coping skills. Secondary outcomes are child quality of life, child general coping skills, child self-perception, parental stress, quality of parent-child interaction, and parental perceived vulnerability. Outcomes are evaluated at baseline, after 6 weeks of treatment, and at a 6 and 12-month follow-up period. The analyses will be performed on the basis of an intention-to-treat population.

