## Methods/design

### Interventions

#### Child intervention 'Op Koers'

'Op Koers' is based on techniques proven to be effective in behavioral and cognitive behavioral programs for children with somatic complaints [14] and in children with behavior and/or anxiety disorders [14]. 'Op Koers' has slightly different versions for two different age groups because of differences in cognitive development and age related topics. The first group consists of primary school children (8-12 years) and the second of adolescents in secondary school (12-18 years). The intervention takes place in the hospital were the child is medically treated, and involves six weekly 90 minutes sessions, and one return session after six months. To stimulate group processes and because of educational reasons groups with a minimum of four and a maximum of eight children are formed. The intervention aims to empower children with CI by teaching the active use of coping strategies. These coping strategies are translated into five learning goals: 1) information seeking and information giving about the disease ('good to know better' principle), 2) use of relaxation during stressful situations (using exercises), 3) increase knowledge of self-management and compliance, 4) enhancement of social competence (group discussions, role playing), and 5) positive thinking (effective use of the Thinking-Feeling-Doing model; replacement of inaccurate thoughts) [14]. During the group sessions the goals are translated into psycho-education (such as informative video's and group discussions), and reinforced and practiced through exercises (such as role-play and board games) and homework assignments. In all sessions age-appropriate examples are used.

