### Outcomes measures

Participating children, and one of their parents, are asked to complete questionnaires at baseline, 6 weeks, 6 months and 12 months after baseline. Primary caregivers are asked to fill in questionnaires and to participate in the parent intervention. All questionnaires are assessed online; participants receive an email with a unique link to the questionnaires. Total duration time for filling in the questionnaires is estimated on 45 minutes for children and 35 minutes for the parents.

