#### Parent-child interaction observation task

Six months after baseline assessment (T2) parent-child dyads are observed with a semi-structured parent-child interaction task. This task is an 30-minute observation paradigm in which parent and child collaborate on three different tasks: guiding marbles through a labyrinth, naming coping solutions for hypothetical situations using three different vignettes, and talking about personal disease related emotions and solutions. The three tasks differ in the level of collaboration and competition between parent and child. Observations of the interaction will be independently coded by trained graduate students, unaware of the child's treatment condition. In a study with 100 children (10-16 years old) with a wide range of psychological problems, this task has shown to be sufficient in identifying individual differences in parental responsiveness and granting autonomy support, child's positive affect and showing autonomy, and dyadic collaboration. Trained master students have shown to be reliable in administering and coding the observations (ICC = .74, range .66-.78) [34].

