### Statistical analyses

The analyses will be performed on the basis of an intention-to-treat population. Treatment effects (group × time) will be assessed with linear mixed model analysis using SPSS. Intraclass correlations will be computed to test possible dependency effects of block randomization [35]. In secondary analyses, mediator variables will be included to investigate which underlying processes in children and families change as a result of the intervention. Moderator variables will be included to examine whether the effects are associated with characteristics of the child and the family (gender, age, medical diagnosis, severity of disease, attendance during group sessions).

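### The first follow-up is tied to treatment in the Abstract but to baseline in the body, and the baseline clock can place it before the six sessions are finished

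*Protocol article*

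**What the plan says.** The Abstract (Methods/design) describes the schedule this way: "Outcomes are evaluated at baseline, after 6 weeks of treatment, and at a 6 and 12-month follow-up period". The first follow-up there is counted from treatment.

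The body counts it from baseline. Procedure says: "In all conditions assessments take place at baseline, 6 weeks, 6 months and 12 months after baseline". Outcomes measures repeats that children and one parent "are asked to complete questionnaires at baseline, 6 weeks, 6 months and 12 months after baseline".

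Procedure then allows a gap before treatment: "Within a month after the baseline measurements, the intervention starts". The section on the child intervention says that the programme "involves six weekly 90 minutes sessions, and one return session after six months".

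The analysis uses all the assessments together: "Treatment effects (group × time) will be assessed with linear mixed model analysis using SPSS" (Statistical analyses). The observation task is described with "Six months after baseline assessment (T2) parent-child dyads are observed", so the 6-week assessment is by implication T1. The article does not use that label itself.

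**The concern.** The two definitions name the same date only if treatment begins on the day of baseline. For any later start, the body's clock runs ahead of the treatment. A block that starts late enough is then measured while its sessions are still under way.

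This assessment is the only one near the end of the weekly sessions; the next is at 6 months. Sessions are given in groups organised by hospital, age group and cohort, so the gap between baseline and first session plausibly differs from block to block. The first follow-up could then pool children who have finished the course with children part-way through it.

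Two readings would suffer. The short-term contrast with the wait-list would tend to be understated. The change from 6 weeks to 6 months would also partly reflect completion of the course. That second point touches a stated aim: the Background expects the parent module to add most at medium and long term, and the Discussion wants to test whether involving parents strengthens lasting effects. A rise after the first follow-up could be taken for such an effect when some of it is simply the remaining sessions.

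**Working it through.** The article states no figure to reproduce. The check is a calendar count.

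**Inputs**
- First follow-up on day 42 after baseline (Procedure; Outcomes measures).
- First session on day *s*, with *s* from 0 to the end of a month, taken as 28 to 31 days (Procedure).
- Six weekly sessions, on days *s* + 7*k* for *k* = 0 to 5, so the last is on day *s* + 35 (Child intervention).

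**Sessions given by day 42** = the number of *k* with *s* + 7*k* ≤ 42, or < 42 if a session on day 42 itself is not counted.

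| First session (day) | Sessions by day 42, counting day 42 | Not counting day 42 | Sixth session (day) | Day 42 relative to sixth session |
|---|---|---|---|---|
| 0 | 6 | 6 | 35 | 7 days after |
| 7 | 6 | 5 | 42 | same day |
| 8 | 5 | 5 | 43 | 1 day before |
| 14 | 5 | 4 | 49 | 7 days before |
| 21 | 4 | 3 | 56 | 14 days before |
| 28 | 3 | 2 | 63 | 21 days before |
| 30 | 2 | 2 | 65 | 23 days before |
| 31 | 2 | 2 | 66 | 24 days before |

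All six sessions are given by day 42 only if *s* + 35 ≤ 42, that is *s* ≤ 7 (*s* ≤ 6 if the sixth must come strictly before).

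**The Abstract's clock.** Six weeks from the first session is day *s* + 42: day 42 for *s* = 0 and day 72 for *s* = 30. The sixth session is always 7 days earlier, so this reading covers the full course for every start date. Wait-list children have no treatment start, however, so the reading needs a stated anchor for them.

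**How common the problem could be.** The article gives no distribution of start dates. Suppose, as an assumption only, that starts are spread evenly over days 0 to 30. Then 8 of 31 start days (26%) allow all six sessions by day 42, or 7 of 31 (23%) under the stricter count. The mean number of sessions given is 136/31 = 4.4, or 132/31 = 4.3.

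**Illustration of dilution.** Assume a full effect of .5 that builds up in proportion to sessions; the article supports neither assumption for this time point.
- Latest start: .5 × 2/6 = .17 to .5 × 3/6 = .25 at the first follow-up.
- Evenly spread starts: .5 × 4.3/6 to .5 × 4.4/6, about .36.
- Simple mean of the three follow-ups, with .5 at the later two: (.36 + .5 + .5)/3 = .45 for evenly spread starts, and .39 to .42 for the latest start.

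**Later assessments.** The sixth session falls on day 66 at the latest, well before 6 months. The 6- and 12-month assessments follow all six weekly sessions on any permitted start.

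**The case against.** The strongest defence is that this is loose wording. The month is an upper limit, not a typical delay, and groups may in practice start within days. The 6 weeks in the body may be shorthand for the post-treatment assessment that the Abstract describes. Figure 1, which is not available here, may show it placed after the sixth session. A common baseline clock is also a defensible choice when one arm never starts treatment: with randomization in blocks within hospital, it keeps elapsed time equal across arms. Any mistiming would therefore tend to understate a short-term effect, not create one.

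Most of this stands, and it limits the size of the point. It does not remove the conflict: the text gives one anchor once and another twice, and a figure could show the intent without making the sentences agree.

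A reader might infer more than the article supports:
- **That children typically have only two or three sessions by then.** That is the limit of the permitted range; actual start dates are not given.
- **That the effect at this point falls to .17 to .25.** Those values need the latest start and proportional build-up. The Sample size section also states its d = .5 for differences between conditions over four measurements, not for the 6-week point.
- **That the first follow-up is unusable, or the main result compromised.** The article does not name 6 weeks as the primary time point, tests group by time over all assessments, and does not assign mediators to this point. The observed parent-child interaction is measured at 6 months.

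**Conclusion.** The point holds as an internal contradiction with a practical consequence. Following Procedure and Outcomes measures as written puts the only near-term assessment before the sixth session for any block that starts more than about 7 days after baseline, and up to about three weeks before it at the latest permitted start. The calendar count rests only on the article's own figures, with a month read as 28 to 31 days. How many children would be affected cannot be determined from the article.

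The consequence is confined to the 6-week contrast, which would tend to be diluted, and to the reading of change between 6 weeks and 6 months. The 6- and 12-month contrasts are not affected, and elapsed time remains equal across arms. This should be fixed, but it does not undermine the trial as a whole.

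**What to change.** Reconcile the passages on one anchor. The preferable one is the end of the six sessions of each block: for example, send the questionnaire link within one week after the sixth session. Send it on the same date to the wait-list children of the same hospital, age group and cohort, so that timing stays equal across arms. State beforehand which date counts if the two intervention groups of a block finish on different days. Correct Procedure and Outcomes measures accordingly. This moves an assessment and leaves treatment unchanged.

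If the baseline clock is kept, correct the Abstract and do not interpret the 6-week contrast as an end-of-treatment effect.

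The cost is small, because the questionnaires are completed online through an emailed link. The interval from baseline will vary between blocks. The study already has ethics approval, so a protocol amendment is needed. The change is best made before the first cohort reaches this assessment; made later, it would leave the first follow-up defined differently across the three cohorts.

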**Figure 1 F1:**
[figure not shown]
**Study procedure in flow diagram**.

### Inclusion and exclusion criteria

For inclusion, children between 8 and 18 years old and suffering from a chronic illness are selected. The term 'chronic illness' refers to illnesses that require at least 6 months of continuous medical care, permanent life style changes and continuous behavioral adaptation to the unpredictable course of the illness [2]. Children who attend special education due to severe learning difficulties are excluded, because for these children an adapted or individual program might fit better to their individual cognitive needs. The final criterion is that children and parents should be able (with help) to fill in Dutch questionnaires.

### Randomization

Participants are randomly allocated to the conditions within their own hospital. For each hospital, the assignment of participants is carried-out by using a block randomization method [17,18]. Interventions are organized at three time points (three cohorts), to spread recruitment over time. An allocation schedule is formulated in which the conditions (separately for each age group) will equally be divided across the centers and cohorts to ensure the number of groups is about the same within each condition. To ensure minimal differences between hospitals, participants will be considered in blocks of 12, 15, 18, 21 and 24 (4 to 8 in each condition), and in each centre heterogeneity of medical diagnosis is guaranteed. An independent researcher makes the allocation schedule using random allocation software.

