### Sample size

The expected effect size and attrition rates are based on former trials that studied the effects of cognitive-behavioral group interventions for children with CI. Generally, psychological interventions for children with CI indicated medium effect sizes (mean ES = 0.71, range = 0.28-3.23, SD = 0.61) [6]. In a study that evaluated cognitive-behavioral group interventions for children with anxiety disorders, enhanced by parental involvement also medium effect sizes were found [19]. Based on four repeated measurements with within-subject correlations of .5, a sample size of 126, 42 in each condition, is necessary to achieve adequate power (.80) to trace differences of medium effect size (d = .5) between the conditions over time at a significance level of .05 [20]. To be able to control for dependency effects (block and centre effects) and taking into account 10% attrition over time, 162 children have to be recruited to reach the required sample size.

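### The stated group × time model uses the baseline score inefficiently and does not commit to the randomisation factors; the loss is precision, not validity

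*Protocol article*

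**What the plan says.** **Allocation.** The Randomization section of the Protocol article states: "Participants are randomly allocated to the conditions within their own hospital". It uses block randomisation and a schedule in which "the conditions (separately for each age group) will equally be divided across the centers and cohorts". Block sizes run from 12 to 24. The Discussion describes the method as stratified.

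**Sample size.** The calculation is "Based on four repeated measurements with within-subject correlations of .5" and arrives at 42 per condition (126 in all) for d = .5, power .80 and a significance level of .05. The target is then raised: "To be able to control for dependency effects (block and centre effects) and taking into account 10% attrition over time, 162 children have to be" enrolled.

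**Analysis.** The Statistical analyses section says: "Treatment effects (group × time) will be assessed with linear mixed model analysis using SPSS". On dependency it says: "Intraclass correlations will be computed to test possible dependency effects of block randomization". It does not say what follows from that test. It names no baseline covariate and no primary-model term for hospital, cohort or age group; age appears among the moderators in secondary analyses. Assessments are at baseline, 6 weeks, 6 months and 12 months, so baseline is one of the four repeated measurements.

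**The concern.** Two features of the stated model deserve attention.

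1. **Baseline.** If baseline is one of the outcomes in a group × time model, each treatment effect is a difference between arms in change from baseline. With a moderate within-child correlation, this carries the full noise of the baseline score into the comparison. A covariate adjustment removes only the part of the outcome that baseline predicts, and has a smaller variance.

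2. **Randomisation factors.** The design balances arms within blocks, and the sample was enlarged to allow control of block and centre effects. The analysis text treats block dependency as something to be tested. With only about 7 to 13 blocks such a test has little power, and whether a design factor is in the model should not hang on it.

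At stake is precision that the stratified design and the baseline assessment have already paid for. It matters most at individual follow-up visits, because medium- and long-term effect is a central question of the trial.

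**Working it through.** **Inputs from the article.** Four measurements (one baseline, three follow-ups); within-child correlation r = .5; d = .5; alpha .05; power .80; 42 per condition; 162 recruited; 10% attrition; seven hospitals, two age groups, three cohorts; blocks of 12 to 24.

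**Assumptions.** Two-sided test (the article does not say), equal correlation between all visits, pairwise comparison of two arms, normal approximation.

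**Step 1: reproduce the plan's figure.** The variance factor of the mean of three follow-ups minus baseline, in units of the outcome variance, is

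(1 + 2r)/3 + 1 − 2r = .667 + 0 = .667.

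The number per arm is 2 × (1.960 + .842)² × .667 / .5² = 41.9, so 42 per arm and 126 in all, with power .801. This matches. At r = .5 the follow-up mean without baseline also has factor (1 + 2r)/3 = .667, so the match does not show which contrast the authors used.

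**Step 2: baseline as covariate.** The factor for the mean of three follow-ups becomes (1 + 2r)/3 − r² = .667 − .25 = .417. For a single follow-up, change from baseline has factor 2(1 − r) = 1.00 and the adjusted score has 1 − r² = .75. In both cases the reduction is (1 − r)² = .25, which shrinks as r approaches 1.

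With SE = √(2 × factor / 42) and power = Φ(.5/SE − 1.96):

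| Contrast | Factor | SE | Power at 42 per arm | Per arm for .80 |
|---|---|---|---|---|
| Follow-up mean, change | .667 | .178 | .80 | 42 |
| Follow-up mean, adjusted | .417 | .141 | .94 | 27 |
| Single visit, change | 1.00 | .218 | .63 | 63 |
| Single visit, adjusted | .75 | .189 | .75 | 48 |

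For the follow-up mean, the detectable d falls from .50 to .50 × √(.417/.667) ≈ .395, about .40.

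**Step 3: what the enlargement pays for.** Attrition alone gives 126/.9 = 140. The target of 162 leaves 162 × .9 = 145.8 evaluable, and 145.8/126 = 1.16. So about 16% more evaluable children than the basic calculation needs are budgeted for dependency effects.

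**Step 4: stratum terms.** The article gives no stratum variances, so the values here are assumptions. A simulation used 12 strata of 12 children (N = 144), three arms and 3,000 replicates per scenario; the simulation error of a .05 rejection rate is √(.05 × .95/3000) ≈ .004.

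| Contrast | Assumed strata | Model SE without / with terms | Type I error without / with |
|---|---|---|---|
| Change | level only, 10% of variance | .167 / .167 | .044 / .043 |
| Change | level only, 20% | .167 / .167 | .049 / .049 |
| Change | level 10%, stratum-by-time .05 | .172 / .167 | .042 / .050 |
| Baseline-adjusted | level only, 20% | .132 / .122 | .045 / .055 |
| Baseline-adjusted | level 10%, stratum-by-time .05 | .139 / .128 | .032 / .046 |

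For the change contrast, level differences between strata cancel within the child. Only differences in course over time remain; in that scenario power for d = .5 is .84 without stratum terms and .85 with them. Once follow-up scores are modelled with baseline as covariate, part of the level difference stays in the error, so stratum terms matter somewhat more.

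**Step 5: can the terms be estimated?** Blocks number between 162/24 = 6.75 and 162/12 = 13.5, or 9 at size 18. Separate terms for hospital (6 df), age group (1) and cohort (2) need 9 df. If each block lies in one hospital, age group and cohort, nine blocks supply only 8 df between them. A block term is always estimable; the three factors separately may not be.

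**The case against.** The strongest reply is that one line in a journal article is being read as a complete model. The article shows that its analysis section is not exhaustive: the Background says type of diagnosis will be tested as a control variable, and Study design says outside treatment will be controlled for, yet neither is listed as a control term under Statistical analyses. The Sample size section states an intent to control block and centre effects. A covariate list may also properly sit in an analysis plan that is not shown.

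This disposes of several stronger readings. A reader might infer that the analysis ignores the stratification, or that stratum terms enter only if the ICC test is positive. The article says neither; it is silent on what the ICC result leads to. A reader might also infer that standard errors are materially too wide. For the stated within-child contrast they are not, unless strata differ appreciably in course over time, and nothing in the article supports a figure for that. Nor is the net direction known, because dependency within therapy groups of four to eight children acts the opposite way.

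On baseline, the reply is that group × time in a mixed model is a standard, valid analysis, that it does use the baseline score, and that the wording does not exclude a model constraining the arms to a common baseline mean, which would recover essentially the same efficiency. It is also true that nothing falls short of the planned power for the follow-up mean, and that the article does not name a single-visit contrast as its test.

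What stands is narrower. The model as written does not claim the available efficiency, and making block dependency a matter of testing sits awkwardly with a sample already enlarged to control it.

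**Conclusion.** The point holds as one of efficiency and commitment. The stated analysis is valid, and its 42 per condition reproduces. There is no bias, no inflated type I error from this source and no wrong figure; a reading of the trial as invalid or underpowered on these grounds is not supported.

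The baseline half carries the weight and uses the plan's own correlation: the variance of the follow-up-mean contrast falls by .25/.667, about 37%, and that of a single-visit contrast by 25%. These figures assume equal correlation of .5 between all visits and a two-sided test, and they compare adjustment with an unconstrained change-from-baseline model.

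The randomisation-factor half is small for the stated contrast: no gain if strata shift only the level, and otherwise a slightly conservative test under assumed variances. Its main value is to settle the model in advance and to bring Statistical analyses into line with Randomization and Sample size.

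**What to change.** In Statistical analyses, replace the model line along these lines:

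- A linear mixed model on the 6-week, 6-month and 12-month scores, with arm, time, arm × time and the baseline score as covariate; or an equivalent model on all four scores with baseline means constrained equal across arms.
- The treatment effect is the arm contrast at each follow-up, or averaged over follow-ups. It should not be the arm × time interaction alone: once baseline is a covariate, that interaction tests only whether the effect differs between follow-ups and would miss a constant benefit.
- Randomisation block is included as a factor (or hospital, age group and cohort where all are estimable), whatever the ICC shows.
- The ICC assessment stays, and dependency within therapy groups is handled as a separate matter. The block terms do not deal with it, and the ICC sentence is the analysis text closest to it.

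Cost: a few sentences and a few degrees of freedom (8 for nine blocks, out of 162 children). No new data are needed and the sample size need not change.
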